## Abstract

**Introduction:**

High-quality shared decision-making (SDM) is a priority of health services, but only achieved in a minority of surgical consultations. Improving SDM for surgical patients may lead to more effective care and moderate the impact of treatment consequences. There is a need to establish effective ways to achieve sustained and large-scale improvements in SDM for all patients whatever their background. The ALPACA Study aims to develop, pilot and evaluate a decision support intervention that uses real-time feedback of patients’ experience of SDM to change patients’ and healthcare professionals’ decision-making processes before adult elective surgery and to improve patient and health service outcomes.

**Methods and analysis:**

This protocol outlines a mixed-methods study, involving diverse stakeholders (adult patients, healthcare professionals, members of the community) and three National Health Service (NHS) trusts in England. Detailed methods for the assessment of the feasibility, usability and stakeholder views of implementing a novel system to monitor the SDM process for surgery automatically and in real time are described. The study will measure the SDM process using validated instruments (CollaboRATE, SDM-Q-9, SHARED-Q10) and will conduct semi-structured interviews and focus groups to examine (1) the feasibility of automated data collection, (2) the usability of the novel system and (3) the views of diverse stakeholders to inform the use of the system to improve SDM. Future phases of this work will complete the development and evaluation of the intervention.

**Ethics and dissemination:**

Ethical approval was granted by the NHS Health Research Authority North West-Liverpool Central Research Ethics Committee (reference: 21/PR/0345). Approval was also granted by North Bristol NHS Trust to undertake quality improvement work (reference: Q80008) overseen by the Consent and SDM Programme Board and reporting to an Executive Assurance Committee.

**Trial registration number:**

ISRCTN17951423; Pre-results.

STRENGTHS AND LIMITATIONS OF THIS STUDYA mixed-methods study design will use a diverse representative sample of surgical patients from a range of National Health Service trusts to determine the feasibility of data collection, the usability of the novel system and understand views of diverse stakeholders to inform use of the system.Recruitment will focus on recognised underserved groups (economically disadvantaged, older age, ethnic minority) from Bristol and Bradford to maximise reach to an ethnically and socioeconomically diverse population.The study uses three validated questionnaires to monitor shared decision-making (CollaboRATE, SDM-Q-9, SHARED-Q10), including first use of the SHARED-Q10 measure in a surgical setting.This study excluded patients without decisional capacity due to distinct requirements and guidance for consent and shared decision-making processes in this population.

## Introduction

Shared decision-making (SDM) is a process where patients are supported to reach decisions in collaboration with health professionals.^1^ Global and United Kingdom (UK) policy,^2–4^ professional and regulatory guidelines^5 6^ recommend SDM in all healthcare settings. Making good decisions is particularly important for the 5 million people per year deciding to have surgery in the UK because, unlike many medical therapies, the effects are usually immediate and irreversible. Ensuring patients and surgeons have discussed accurate information about all options and their consequences, exchanged their reasoning about, and preferences for, each option, and agreed the treatment plan is essential to a good SDM process.

Evidence shows there is scope to improve SDM for surgery. A systematic review of 22 surgical studies found that only 36% of 13 176 patients perceived their consultation as shared.^7^ Other systematic reviews show that surgeons underestimate patients’ information needs,^8^ and patients do not receive desired information before surgery.^9^ Major surgical risks go undisclosed,^10^ and patients report feeling uninformed^11^ and want more involvement in decision-making.^12^ The impact of these deficiencies is inadequately understood. It is thought that improving SDM processes may lead to more effective care through enhanced clinician–patient reasoning,^13^ thereby supporting treatment choices with greater benefit/harm ratios^8^ and reducing overall use of health services.^14 15^ High-quality SDM may also moderate the impact of treatment harms through more realistic treatment expectations^16 17^ and improved self-management.^18^

Guidelines for the implementation of SDM have been recently published by the National Institute for Health and Care Excellence (NICE) that includes best evidence from a Cochrane review^9^ and consultation with 454 stakeholders. It concluded that a combination of interventions to support organisations, clinicians and patients is needed, but the evidence for these interventions is often poor.^19^ Key priority areas were identified for future research, including generating evidence about how to: (1) sustain SDM implementation at an organisation/health service level, (2) measure the effectiveness of the SDM process for different contexts/settings/people, and (3) ensure the SDM process is inclusive of people from diverse backgrounds (eg, ethnic minorities, persons of lower health literacy or income backgrounds).

The ALPACA Study aims to address these deficiencies. We will develop, pilot and evaluate a decision support intervention that uses real-time feedback of patient experiences of the SDM process to impact patient and professional decision-making processes before adult elective surgery and improve patient and health service outcomes. The intervention will include (1) efficient, real-time evaluation of patient experiences of SDM at scale, (2) timely feedback of individual patient-reported experiences of SDM to care teams before surgery and (3) activities supporting meaningful change in patient and professional decision-making about surgery, individually and together.

This project aims to enable surgical teams to remedy deficiencies in the SDM process before surgery and thereby addresses NICE research priorities to detect such deficits reported by the patient. The intervention will be deliverable at scale to create sustained improvement in SDM through system-wide changes in decision-making processes facilitated by continuous patient-reported feedback. It will be co-created with patients with a focus on inclusivity of recognised underserved groups. Developing methods for efficient evaluation of the SDM process will make measurement of SDM outcomes more consistent and meaningful.

### Aim and objectives

The overall aim of this project is to develop, pilot and evaluate a decision support intervention that uses real-time feedback of patient experience of SDM to change patient and professional decision-making processes before adult elective surgery and improve patient and health service outcomes. There are three phases with the following objectives:

Phase 1: assess the feasibility, usability and stakeholder views of implementing an automated system to monitor the SDM process for surgery in real time.

Phase 2: co-develop and refine the intervention with patients and professionals to understand how the intervention works, for whom and in what context using findings from phase 1.

Phase 3: evaluate the effectiveness, cost-effectiveness and implementation of the intervention to improve patient and health service outcomes in the English National Health Service (NHS).

This protocol describes phase 1. Details of subsequent phases which will complete the development (phase 2) and evaluation of the intervention (phase 3) will be described in future publications.

## Methods

The project will employ mixed-methods to develop a complex intervention comprising multiple components that will impact a wide range of stakeholders and system processes. The overall aim to develop and evaluate the intervention will be conducted according to Medical Research Council (MRC) guidelines.^20^ Phase 1 reported here is consistent with the MRC framework’s feasibility phase, with consideration of the core elements critical for complex intervention research. Any qualitative elements will be reported in accordance with the Consolidated criteria for Reporting Qualitative research guidelines.^21^

### Conceptualisation

There is no unified definition of SDM. A systematic review identified 40 SDM models currently available with 53 different elements clustered in 24 overarching components.^1^ Components present in more than half of models were: ‘describe treatment options’ (88% of models); ‘make a decision’ (75%); ‘patient preferences’ (68%); ‘tailor information’ (65%); ‘deliberate’ (58%); ‘create choice awareness’ (55%) and ‘learn about the patient’ (55%).

This study will conceptualise SDM using the ‘Three Talk model’ (2012),^22^ later refined to ‘Implement-SDM’ (2019).^23^ This single-component model provides a guide for enhancing health professional communication to deliver SDM, and is the most highly referenced model (>1800 citations, Web of Science). It involves three key steps consistent with other models of SDM: (1) introduction of choice, (2) describing options and (3) helping patients explore preferences and make decisions. This was the chosen model for an NHS MAGIC Programme^7^ and is recommended in NICE guidelines.^24^

### Setting

Research will be conducted at three UK hospital trusts (North Bristol Trust/NBT, University Hospitals Bristol and Weston NHS Foundation Trust/UHBWFT and Bradford Teaching Hospitals NHS Foundation Trust/BTHFT) alongside quality improvement programmes to improve SDM. NBT is one of the largest acute NHS trusts in the UK.^25^ It provides a full range of acute clinical care for both local and regional clinical commissioning groups in South-West England. Specialised services are provided through NHS England, Welsh Health Boards and Welsh Specialist Commissioners. Services provided include elective and emergency gastrointestinal surgery, obstetrics and gynaecology, as well as specialist regional services in urology, neurosciences, trauma and orthopaedic and vascular surgery. One UHBWFT department is included as the South-West England regional cardiac surgical centre. BTHFT is an acute trust in the North of England with a full range of elective and emergency surgical services. Bristol and Bradford were purposively selected to maximise reach to ensure a diverse representative sample is included (eg, 26.8% classed as Asian or Asian British, compared with 5.5% in Bristol).

#### Phase 1: assess the feasibility, usability and stakeholder views of implementing an automated system to monitor the SDM process for surgery in real time

Phase 1 will determine whether it is feasible and acceptable to monitor SDM processes for surgery automatically and in real time using a novel electronic system. Objectives are to explore:

1.1 Feasibility of automated data collection.

1.2 Usability of the electronic measurement system.

1.3 Views of diverse stakeholders to inform the use of the system to improve SDM.

Each objective comprises separate methods which are described in turn below. This phase is expected to continue until June 2025.

### Feasibility of automated data collection

Feasibility assessment is designed to establish the feasibility of automated real-time evaluation of patient experiences of SDM at scale and will identify opportunities to optimise recruitment and data collection.

### Participants

All patients over the age of 18 years who have been booked for planned vascular, gastrointestinal, urological, neurosurgical, gynaecological, breast, cardiac and orthopaedic surgical procedures at participating hospitals will be eligible to participate. Surgical departments have been selected to be broadly representative of a diverse range of surgical specialties. Excluded will be patients under the age of 18 years, those without decisional capacity to consent for medical procedures, or undergoing unplanned (emergency) surgery or endoscopic procedures. Data related to eligibility criteria are routinely collected through electronic patient record (EPR) systems.

### Measurement of patient experience

Real-time measurement of patient experiences of the process of SDM will be facilitated by a secure, automated system procured through a third-party provider approved by NHS trusts. The system is a customisable off-the-shelf electronic patient-reported outcome measurement software and has previously been used for electronic data capture in other countries. Eligible patients will be identified through EPR using algorithms developed in collaboration with the software provider. Structured data queries will be designed to extract details of patients booked for eligible procedures. Queries will be designed to run automatically, securely transferring data from the hospital to the software provider daily to account for changes in scheduling. The automated system will send three validated SDM measurement instruments within 1 day after surgery booking (real-time baseline measurement). This time point in the decision-making process was chosen as a pragmatic point in time to represent patients’ cumulative experiences of SDM for surgery which may include discussions with surgeons, physicians, general practitioners, nurses, family and friends. The selected measurement instruments will be operationalised into an online survey and administered via short messaging service (SMS) or email. A reciprocal data feed will securely return patients’ survey responses immediately to the hospital data warehouse for secure storage (real-time analysis and feedback). Follow-up measures are sent within 1 day before surgery by either SMS or email (real-time follow-up measurement). A schematic of the process and intervention aims is illustrated in figure 1.

**Figure 1 F1:**
[figure not shown]
Schematic of measurement process. SDM, shared decision-making; SMS, short messaging service.

Selection of three SDM measures was made through discussions within the study team and was informed by a systematic review of SDM measurement instruments using COSMIN (consensus-based standards for the selection of health measurement instruments) methods,^26^ national guidelines^19^ and recommendations and use within NHS clinical practice.^27–29^ The CollaboRATE instrument is a validated three-item patient-reported measure assessing the extent of SDM experienced by patients.^30^ Assessment of the instrument using COSMIN methods demonstrated acceptable discriminative validity, concurrent validity, intrarater reliability and sensitivity to change.^26^ It has been used in excess of 40 studies,^31^ including evaluations of quality improvement projects in surgery.^32^ The SDM-Q-9 instrument is a validated nine-item patient-reported measure that evaluates their perceptions of involvement in the decision-making process.^33^ It has been widely used in interventional studies and demonstrates good reliability and structural validity.^26 33^ Systematic review evidence recommended use of SDM-Q-9 for surgery.^34^ The SHARED-Q10 instrument is a 10-item patient-reported measure to assess patient perceptions of information provided, involvement in consultations and agreement with the decision made.^35^ This measure is included because it was developed, validated and used in an NHS quality improvement programme^36 37^ and evaluates domains beyond patient perception of professional communication. Complete measurement instruments can be found in online supplemental figures 1–3.

10.1136/bmjopen-2023-079155.supp1Supplementary data

### Analysis

Feasibility of real-time monitoring will be evaluated by analysis of overall recruitment rate, response rates and time to response for the SDM measures at baseline and follow-up. Response rates will be presented as a number and percentage based on patients who completed the measures (eg, completed all three items of the CollaboRATE instrument). Issues of equality, diversity and inclusion will be explored by examining the correlation between responders/non-responders and sociodemographic patient variables extracted from EPR.

Relationships between responders and non-responders and clinical and sociodemographic details will be explored using univariable and multivariable logistic regression. Included will be age, sex, ethnicity, Index of Multiple Deprivation, and clinical and treatment parameters (eg, operation (three-digit Classification of Interventions and Procedures (OPCS) code), diagnosis (International Statistical Classification of Diseases and Related Health Problems (ICD-10) code), date of booking, specialty, number of outpatient appointments in relevant specialty, number and length of hospital inpatient episode in relevant specialty). Index of Multiple Deprivation will be derived by lower layer super output area for individuals’ postcode. All variables will be extracted from routinely collected data in EPR.

In addition, the study team will document any relevant technical, financial, administrative and logistical observations throughout the study and pertinent challenges using shared electronic records (eg, Microsoft Office suite). Any learning points will be descriptively summarised.

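### Hospital site is not among the covariates stated for the responder model, although the sites were chosen for differing ethnic mix, so the ethnicity association may be confounded by site

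*Protocol article*

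**What the plan says.** The Analysis section under feasibility of automated data collection sets out the model: "Relationships between responders and non-responders and clinical and sociodemographic details will be explored using univariable and multivariable logistic regression". It then gives the covariates: "Included will be age, sex, ethnicity, Index of Multiple Deprivation, and clinical and treatment parameters". The examples attached to the clinical and treatment parameters are operation code, diagnosis code, and "date of booking, specialty, number of outpatient appointments in relevant specialty, number and length of hospital inpatient episode in relevant specialty". Trust, hospital and city are not named, either as covariates or as strata.

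The same section gives the equality purpose of comparing responders with non-responders: "Issues of equality, diversity and inclusion will be explored by examining the correlation between responders/non-responders and sociodemographic patient variables extracted from EPR".

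The Setting section describes the sites: "Research will be conducted at three UK hospital trusts", two of them in Bristol and one in Bradford. It gives the reason for the choice, "Bristol and Bradford were purposively selected to maximise reach to ensure a diverse representative sample is included", and supports it with "26.8% classed as Asian or Asian British, compared with 5.5% in Bristol"; by context the first figure is Bradford's. It adds: "One UHBWFT department is included as the South-West England regional cardiac surgical centre".

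**The concern.** A covariate confounds an association when it is related to both the exposure and the outcome. Here the exposure of interest is ethnicity and the outcome is responding to the survey. The choice of sites relates city to ethnicity deliberately. City could also be related to response, because invitations depend on data extracted and transferred from hospital records, and because the work runs alongside quality improvement programmes that may be at different stages.

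Specialty, which is among the examples, helps only in part. It largely identifies University Hospitals Bristol and Weston, which contributes one cardiac department. It cannot separate North Bristol from Bradford within the specialties that both provide, and that contrast carries the ethnic difference.

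At stake is how an ethnicity coefficient is read. A lower response at one hospital and a lower response among ethnic minority patients within each hospital are different findings. The model as stated may not tell them apart, and this is the only quantitative equality analysis that the article describes.

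**Working it through.** The article states no expected response rate, sample size or power for this model, so there is no figure of its own to reproduce. The check asks how large an ethnicity association could arise from site alone.

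**Inputs from the Setting section:** Asian or Asian British share 0.268 (Bradford) and 0.055 (Bristol). These read as area figures, not shares of booked surgical patients.

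**Assumed, not in the document:** Bradford's share of bookings *w*, the response rate in each city, and no ethnic difference in response within either city.

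**Step 1: link between city and ethnicity.**
(0.268/0.732) / (0.055/0.945) = 0.3661/0.0582 = 6.3.

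**Step 2: where each group's patients come from, with *w* = 0.5.**
- Bradford share among Asian patients: 0.268/(0.268 + 0.055) = 0.830
- Bradford share among other patients: 0.732/(0.732 + 0.945) = 0.436

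**Step 3: crude response, with 40% in Bristol and 25% in Bradford.**
- Asian: 0.830 × 0.25 + 0.170 × 0.40 = 0.276
- Other: 0.436 × 0.25 + 0.564 × 0.40 = 0.335
- Odds ratio: (0.276/0.724) / (0.335/0.665) = 0.76

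Within each city the odds ratio is 1.00 by assumption, so the whole of the 0.76 comes from leaving out site.

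**Step 4: range over assumed response rates (*w* = 0.5).**

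| Bristol | Bradford | Ethnicity odds ratio without site |
|---|---|---|
| 30% | 30% | 1.00 |
| 30% | 25% | 0.91 |
| 40% | 30% | 0.84 |
| 30% | 20% | 0.80 |
| 40% | 25% | 0.76 |
| 50% | 25% | 0.64 |
| 30% | 40% | 1.19 |

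The booking split matters less. With *w* = 0.3, the 40% versus 25% case gives 0.75.

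**Step 5: would it be noticed as a finding?** Take 30% versus 20% response and Bradford at one third of patients. Then 71% of Asian patients and 28% of others come from Bradford, crude response is 22.9% versus 27.2%, and the odds ratio is 0.80. The chance that a two-sided 5% test calls this significant is about 29% with 2,000 patients and 63% with 5,000; both totals are assumed.

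These are two-by-two calculations with no other covariate. They show what site alone could do. They do not estimate the bias left after specialty, procedure, diagnosis, deprivation and prior contacts are in the model.

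**The case against.** The strongest reply is that a condensed article has been read as a full specification. The clinical and treatment list is introduced as examples, and a fuller plan may include trust. This stands in part: one can say that trust is not named, not that it is excluded. But the examples qualify only the clinical and treatment parameters, and trust is not plainly one of those. The stated list is detailed enough to reach three-digit procedure codes and still leaves out a factor on which the sites were selected.

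Second, confounding needs response to differ by site after the other covariates, and the article gives no response rates. That stands. A 25% versus 30% difference moves the odds ratio only to about 0.9, and equal response moves it not at all. Some covariates may also act as partial stand-ins for site.

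Third, the crude gap is itself of interest. If fewer minority patients respond because their hospital has a low response, that is still unequal reach, and the planned univariable analysis would show it. This stands too, and is why the crude figures should be kept.

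A reader might infer more: that site differences are bound to be reported as effects of both ethnicity and deprivation, and that Phase 2 would then address the wrong cause. The article does not support this. It gives no figure linking deprivation to trust. It does not say that each trust has its own record system or programme; it describes one measurement system from one provider. Phase 2 also draws on the qualitative work, and the team will record technical and logistical observations through which site problems could come to light.

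**Conclusion.** The point holds in conditional form. Site is absent from the stated covariates, the article's own figures tie ethnicity to city with an odds ratio of about 6.3, and specialty does not separate North Bristol from Bradford where they share specialties. The ethnicity association may therefore be confounded by site.

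The size is illustrative only. Under the assumed rates, spurious odds ratios run from 0.64 to 1.19, with 0.76 for 40% in Bristol against 25% in Bradford and 1.00 for equal response. These rest on invented response rates and booking splits, on apparently area-level ethnicity figures, and on no adjustment for the covariates that are planned.

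No conclusion is drawn about deprivation, because nothing in the article ties it to site. Since the analysis is exploratory, belongs to a feasibility phase and carries no decision threshold, this is a change that should be made because it is cheap; it does not undermine the study.

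**What to change.** Add a Bristol/Bradford term, alongside specialty, to the multivariable responder models at both baseline and follow-up. A separate term for University Hospitals Bristol and Weston may be collinear with cardiac specialty, because that trust contributes cardiac surgery only; a city term with specialty avoids this.

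Report response by ethnicity within site, next to the crude response by ethnicity. State that the crude figures describe overall reach and the adjusted estimates describe gaps within a site.

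The cost is one model term and one table, with no new data, since each patient's hospital is known. The limitation is that the adjusted estimate speaks only to within-site differences, so it should not replace the crude comparison. If a fuller analysis plan already includes site, a sentence saying so is enough.
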